### Interventions

The individuals of both groups will participate in 14 training sessions (60 min, two times per week), during the “on” phase of dopaminergic medication.

The interventions were designed in order to guarantee the same intensity and quantity of exercises for both groups. The intensity of both group interventions will be adjusted to achieve moderate intensity. We hypothesize that both interventions will motivate the participants in different ways. As conventional physical therapy will be performed in groups, the social aspect will probably be strong in this group, while the novelty of the technology and the amusing nature of the interactive video games may motivate the participants of this group.

#### EPG-based training (control group)

The intervention of the control group (CG) will be developed in accordance with the practice recommendations in the guidelines for rehabilitation in Parkinson’s disease [8]. Sessions will be conducted by a trained physical therapist with a maximum of 20 participants and an instructor-to-participant ratio of 1:2.

The protocol will be structured in order to stimulate (1) muscle flexibility, (2) muscle strength, (3) static and dynamic balance, (4) physical fitness, and (5) transfer through cognitive movement strategies (see Table 2 for details).

**Table 2 Tab2:** Control group exercise intervention description

Modality	Format	Time	Exercises	Intensity	Examples of exercises
Warm up	Group	5 min	Anterior-posterior gait Lateral gait	N/A	Gait training in association with active movements of the upper limbs Dual task training associating cognitive and motor activities
Balance	Group	15 min	Stable and unstable surfaces Progressive levels of complexities in reducing the base of support With visual and auditory cues	N/A	Tandem position Standing on one leg Raising body on the forefoot Without visual afferent (open and closed eyes)
Physical conditioning	Free rhythm set to music	15 min	Gait with change in speed Gait bypassing and overcoming obstacles Circuit	Intensity of the exercises; will use the Borg scale and heart rate	Up and down stairs Multiple direction changes “Zig-zag” movements Walk in tandem
Strength	Individual training	10 min	Concentric isotonic exercises in the sitting or supine position	Three sets of 10 repetitions with elastic bands or weights on the ankles 60 s intervals	Trunk extensors, scapular stabilizers, knee extensors, and hip abductors and extensors
Postural transfers training	Group	5 min	Movement fragmentation conducting the training activities approaching the day-to-day	Requested each subsequent session to repeat the trained movement	Get up and sit down in the chair Get up and lie in bed Get up from the floor
Flexibility and cooldown	Group	5 min	Static muscle stretching in sitting or supine position	3 RPE 30 s	Cervical and trunk extensors, shoulder flexors, elbow extensors, and flexors of the hip and knee

N/A not applicable, RPE repetitions

A comprehensive exercise program will be designed, with a focus on multiple systems involved in postural control, such as postural reactions, sensory integration, and biomechanical constraints. This program will also include gait training in dual tasks and emphasizing of the swing phase, as well as practice for fall-prone function.

The sessions will begin with 5 min of warming exercises in order to prepare individuals for the next exercises. The static and dynamic balance training will be taught for 15 min to perform specific exercises that challenge balance.

Physical conditioning will be conducted for 15 min. In order to assess the intensity of the exercises, we will use the Borg scale [28], which measures the effort level of the subject, as well as heart rate. Both measurements will be used before and after aerobic training. Muscle strength training will be performed for 15 min and will include progressive weight training involving the major muscle groups.

Training postural transfers will be performed for 10 min through specific daily activities that hinder the independence of individuals with PD. Finally, in the last 5 min, flexibility training will be performed in order to relax the muscles and cool down.

#### Kinect adventure-based training (experimental group)

The experimental group (EG) will practice, individually and randomly, four games using the Kinect Adventure program for Xbox 360, developed by Microsoft. The selection of games was done based on a previous pilot study [16].

The individuals will practice five attempt games: (1) *20,000 Leaks*, (2) *Space Pop*, (3) *Reflex Ridge*, and (4) *River Rush*. Table 3 shows the training schedule for the games, together with their motor and cognitive demands. The trained physical therapists that will supervise the practice with the games will use the same verbal instructions during the sessions.

**Table 3 Tab3:** Experimental group exercise intervention description

Game training	Main motor demands	Main cognitive demands
20,000 Leaks	Constant displacement of the individual’s center of mass through movement of the upper limbs and neck Crouching Jumps Multidirectional steps	Fast reaction time Immediate planning and execution Visuospatial attention Dual task
Space Pop	Multidirectional steps Transference of weight between lower limbs Constant displacement of the individual’s center of mass Movement of upper limbs	Immediate planning and execution Visuospatial attention Fast reaction time Dual task
Reflex Ridge	Crouching Jumps Lateral displacement of the center of mass Side steps	Fast reaction time Immediate planning and execution Decision-making Shifting of attention
River Rush	Lateral displacement of the center of mass Crouching Jumps Side steps	Fast reaction time Immediate planning and execution Decision-making Shifting of attention

Adapted from Mendes et al. (2015, p.71) [32]

On the first day of training, there will be a demonstration of each game for the subject. Thereafter, individuals will have two attempts to familiarize themselves with the game and will receive the examiner’s instructions in order to correctly perform the movement to achieve the goal of the game.

After the familiarization phase, individuals will perform the training of the games for 14 sessions, without the interference from the physical therapist. The scores on the games will be recorded in each session of training. After 30 days of training, individuals will perform retention test that will consist of performing another block with five attempts for each game.

Below is the explanation of the steps of the research contained in Table 4, showing the content for the schedule of enrollment, interventions, and assessments.

**Table 4 Tab4:** Content for the schedule of enrollment, interventions, and assessments

	Study period				
Time point	Day 1	Day 2	Days 3 to 16	Day 17	Day 47
Enrollment	X				
Eligibility screen	X				
Informed consent	X				
Allocation	X				
Interventions			X		
EG			X		
CG			X		
Assessments		X		X	X
Initial assessment (Pre)		X			
Final assessment (Post)				X	
Follow-up assessment					X

*EG* experimental group (Kinect adventure-based training), *CG* control group (European Physiotherapy Guideline-based Training)

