**Methods/design:**

A single-blind, parallel, randomized, controlled feasibility trial will be conducted with a sample of 32 individuals diagnosed with idiopathic PD. Participants will be allocated into control group (CG) and experimental group (EG). The intervention of the CG will be conventional physical therapy, and the intervention of the EG will be a supervised practice of five Kinect games. Both groups will perform 14 sessions of 1 h each one, twice a week over 7 weeks. Process outcomes will be safety, feasibility, adherence, and acceptability. Safety will be assessed by the proportion of participants who experienced intervention-related adverse events or any serious adverse event during the study period. Feasibility will be assessed through the scores of the games recorded in all training sessions. Adherence will be assessed through the participant’s attendance. Acceptability will be the motivation of the participants regarding the interventions. Clinical outcomes will be (1) postural control, (2) cognitive function, (3) balance, (4) gait, and (5) QoL. Individuals will be assessed pre- and post-interventions and after 30 days by a blinded evaluator.

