### Outcome measures

Individuals will be evaluated during the “on” period by two blinded, trained physical therapists. The evaluators will be blinded to the type of intervention that individuals will receive. Individuals will be oriented to not comment to the evaluators about any details of the intervention that they will receive. In compliance with the pharmacodynamics of levodopa (onset is 20 to 40 min and duration of effect is 2 to 4 h after medication), individuals will be evaluated in the period of 2 h after medication, according to Lipp et al. [20]. This is the time at which the individual had better engine performance related to the effect of levodopa.

Table 1 details the outcome measures that will be used to assess the treatment effects. All measurements will be taken at baseline (week 0), at the end of the intervention (week 7), and 30 days after the second evaluation (follow-up). For a month after the intervention, the individuals will be instructed to not begin any new physical activity in order to not interfere in the evaluation of the long-lasting effects of the intervention.

**Table 1 Tab1:** Summary of the outcome measures to be used in the study design

Outcome	Measurement tool
Primary outcomes	
Center of pressure and limits of stability	Posturography through the Balance Rehabilitation Unit
Secondary outcomes	
Postural control	Mini Balance Evaluation Systems Test
Functional mobility	Dynamic Gait Index and Functional Gait Assessment
Physical functioning	Five Times Sit-to-Stand Test and 10-Meter Walk Test
Cognition	Montreal Cognitive Scale
Quality of life	Brazilian version of the Parkinson’s Disease Questionnaire

Scales that will be used in the study protocol

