Cognition will be evaluated by the Montreal Cognitive Scale (MoCA). The instrument assesses different cognitive domains, such as visuospatial and executive functions, namely, memory, attention, language, abstraction, delayed recall, and guidance. The total score of the scale is 30, and scores equal to or higher than 26 indicate normal performance [26].

Quality of life will be assessed by the Brazilian version of the Parkinson’s Disease Questionnaire (PDQ-39). It comprises 39 items divided into eight dimensions: mobility, activities of daily living, emotional well-being, stigma, social support, cognition, communication, and body of discomfort. Each item is scored from zero to four. The overall score ranges from zero (no problem) to 100 (maximum problem), but lower scores indicate better perception by the individual of their quality of life [27].

To evaluate the performance game, the score for each game will be compared in each session, comparing the first session (pretest) with the last session (posttest) and retention (30 days after).

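### The Kinect-only retention block falls on or before the 30-day clinical follow-up under the stated intervals, and nothing requires the clinical assessments to come first

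*Protocol article*

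**What the plan says.** The Kinect training section of the protocol article sets a game retention test for the experimental group: "After 30 days of training, individuals will perform retention test that will consist of performing another block with five attempts for each game". The Clinical outcomes section describes the use of the scores, "comparing the first session (pretest) with the last session (posttest) and retention (30 days after"). The nearest event to which that interval can refer is the last session.

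The clinical assessments are timed from a different event. Under Outcome measures, measurements after baseline are taken "at the end of the intervention (week 7), and 30 days after the second evaluation (follow-up"). Table 4 shows interventions on Days 3 to 16, the final assessment on Day 17 and the follow-up assessment on Day 47. It has no row or day for the retention test.

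The section on the control group's training describes no session at 30 days. For the month after the intervention, Outcome measures adds that "the individuals will be instructed to not begin any new physical activity in order to not interfere in the evaluation of the long-lasting effects".

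**The concern.** The retention test is a measurement, but it is also practice. Table 3 lists crouching, jumps, multidirectional steps, displacement of the center of mass and dual-task demands among the games' content. The clinical follow-up measures center-of-pressure sway, limits of stability and dual-task standing; the center of pressure and limits of stability are the primary outcomes in Table 1. A block of play shortly before those tests could help through refreshed practice or hurt through fatigue, and it would do so in one arm only.

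The follow-up is meant to show what lasts after a month without the intervention, and the protocol asks participants to protect that month. If the block comes first, the between-arm difference at 30 days mixes persistence with a recent exposure. The estimate will also be reused: the Statistical analysis section includes follow-up in the effect-size work, and the Discussion says that the results will be used to size a larger trial.

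**Working it through.** **Inputs.** Last training day 16, final assessment Day 17 and follow-up Day 47 (Table 4). Retention interval 30 days (Kinect training and Clinical outcomes sections). Follow-up interval 30 days from the second evaluation (Outcome measures). Five attempts per game (Kinect training section).

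**Step 1: reproduce the plan's own figure.** Follow-up = final assessment + 30 = 17 + 30 = Day 47, which agrees with Table 4.

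**Step 2: the retention test on the same labels.** Retention = last session + 30 = 16 + 30 = Day 46, one day before follow-up. This one-day gap should not be relied on. Days 3 to 16 are 16 − 3 + 1 = 14 days for 14 sessions, whereas the Abstract says: "Both groups will perform 14 sessions of 1 h each one, twice a week over 7 weeks". Up to Day 17, Table 4's days can only be session or visit numbers, so adding 30 calendar days to them does not give a real date.

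**Step 3: remove the dependence on Table 4.** Let L be the calendar day of the last session and k the lag in days to the second evaluation, with k at least 0.

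- Retention = L + 30
- Follow-up = (L + k) + 30
- Gap = follow-up − retention = k

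As an illustration, assume two sessions a week starting on Day 3. There are 13 gaps between 14 sessions. Gaps alternating 3 and 4 days give L = 3 + 7 x 3 + 6 x 4 = 48. Gaps alternating 2 and 5 days give L = 3 + 7 x 2 + 6 x 5 = 47.

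| Lag k (assumed) | L = 48: retention / follow-up | L = 47: retention / follow-up |
|---|---|---|
| 0 | 78 / 78 | 77 / 77 |
| 1 | 78 / 79 | 77 / 78 |
| 7 | 78 / 85 | 77 / 84 |

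With nominal intervals the block is never later than follow-up. It is strictly earlier if k is at least 1. If k = 0, both fall on one day and their order is open.

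**Step 4: size of the exposure.** The Kinect section says: "The experimental group (EG) will practice, individually and randomly, four games using the Kinect Adventure program for Xbox 360". Four games x 5 attempts = 20 attempts per participant in the Kinect arm and 0 in the control arm. The Abstract speaks of five games, which would give 5 x 5 = 25. If one block is counted as one session (an assumption), it adds 1/14 = 7.1% to the Kinect arm's exposure. That is a ratio of exposure and says nothing about the size of a bias.

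**The case against.** The strongest reply is that the protocol never says the retention test comes first. It gives that test no date. A start after 30 days sets no upper limit, and the only contact in Table 4 after the final assessment is the follow-up visit. The most economical reading is that both are done at that visit in an unstated order, and test order within a visit is the kind of detail that an article leaves to the full protocol. This part stands: the documents do not establish that the block precedes the clinical tests.

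Two further replies also stand. The instruction about new activity concerns what participants take up themselves, so a trial-administered test on familiar games does not breach its wording. The statement "The interventions were designed in order to guarantee the same intensity and quantity of exercises for both groups" is about the training programme, and a game score can only be collected in the Kinect arm. Neither sentence is contradicted.

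The reply does not dispose of the point. The article itself gives both intervals, the content of the block and the schedule table. Followed as written, the intervals place the block on or before the follow-up day, and no rule guards against its coming first. Even on a single visit the order matters, because Outcome measures ties the assessments to the 2 h after medication, and a block played first could use part of that window in one arm only.

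**Conclusion.** The point holds as a scheduling weakness. One arm performs 20 game attempts at nominally the same time as the 30-day clinical follow-up, the stated intervals put those attempts on or before that day, and nothing puts the clinical assessments first. The 30-day between-arm comparison may therefore follow a fresh exposure in the Kinect arm only. This rests on two assumptions: that both intervals are kept at about 30 days, and that the retention interval runs from the end of training.

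A reader might infer more, and the documents do not support it:

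- **That retention is on Day 46, the day before follow-up.** That date comes from adding calendar days to session numbers and appears nowhere in the protocol.
- **That the follow-up comparison is known to be biased.** Neither the sign nor the size of an effect can be derived.
- **That evaluator blinding is broken.** This would need a shared visit with the console in the evaluators' view, and no section describes one. It is a risk to close off.

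The week-7 comparison, the attendance data and the training-session scores are not affected. The change is still worth making, because the 30-day estimates are meant to inform a later trial and the remedy costs almost nothing.

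**What to change.** Add a row for the retention test to Table 4, Kinect arm only, tied to the follow-up visit. In the Kinect training section, state that it is performed only after all blinded follow-up assessments for that participant have been completed and recorded, and out of the evaluators' sight. Use the same reference event for both 30-day intervals so that the retention test cannot come first.

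This needs no new procedure. The retention interval for game scores may lengthen by about the lag k between the last session and the post-intervention assessment, for example by one day if k = 1. The report should give the actual interval.

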## Methods/design

### Trial design

This study will be a single-blind, parallel-group, randomized controlled feasibility trial. Participants will provide written informed consent prior to taking part in the study. The protocol will follow the CONSORT guidelines for reporting of non-pharmacological interventions.

The study was approved by the Ethics Committee of the Institute of Psychology, University of São Paulo, Brazil, number 1.506.842, and registered in ensaiosclinicos.gov (RBR-27kqv5). The current study was developed based on Standard Protocol Items: Recommendations for Interventional Trials (SPIRIT) (Additional file 1).

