### Randomization, allocation concealment, and blinding

The participants who fulfill the inclusion criteria will be randomly assigned to one of two groups (experimental or control group) with the same number of participants. Stratified randomization will be achieved by generating a separate block for each stage of PD stages (I, II and III). After all, individuals have been identified and assigned into the blocks, simple randomization will be performed within each block to assign individuals to one of the groups (EG or CG) [31]. Two physical therapists blinded to treatment allocation will record all measurements. The evaluators will be blinded to the type of intervention that individuals will receive. Individuals will be oriented to not comment to the evaluators about any details of the intervention that they will receive.

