### Statistical analysis

The data analysis for the randomized controlled feasibility trial will be undertaken on an intention-to-treat basis. Demographic data will be presented to evaluate baseline comparability of the groups. Descriptive statistics will be used to characterize the groups at baseline and to present feasibility outcomes. Comparisons of the clinical outcomes between CG and EG will be performed to investigate the feasibility of this trial and to calculate estimates for likely effect sizes and 95% confidence intervals. Differences between the two groups will be presented as an unadjusted mean difference for continuous variables with their associated 95% confidence intervals; effect size will be calculated for paired *t*-test and *p* value with an alpha of 0.05, power of 0.8, and 0.5 correlations between baseline, at the end of the trial, and at follow-up. At the end of the study, data collection and statistical code will be publicly available, while maintaining the anonymity of the participants. All data will be analyzed using SPSS software version 22 (SPSS, Chicago, Illinois).

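### Table 4 allocates participants on Day 1 and takes the baseline assessment on Day 2, and nothing withholds the assignment in between, so participants may know their arm at baseline

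*Protocol article*

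**What the plan says.** Table 4 (schedule of enrollment, interventions, and assessments) puts enrollment, eligibility screen, consent and allocation under Day 1. The row beginning "Initial assessment (Pre" is ticked under Day 2, the interventions under Days 3 to 16, the final assessment under Day 17 and the follow-up under Day 47.

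The section Outcome measures fixes the assessment times without relating them to randomization: "All measurements will be taken at baseline (week 0), at the end of the intervention (week 7), and 30 days after the second evaluation (follow-up").

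The section Randomization, allocation concealment, and blinding begins: "The participants who fulfill the inclusion criteria will be randomly assigned to one of two groups". After sorting by disease stage, "simple randomization will be performed within each block to assign individuals to one of the groups (EG or CG"). Completion of the baseline assessment is not named as a condition.

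On blinding, Trial design states: "This study will be a single-blind, parallel-group, randomized controlled feasibility trial". The persons blinded are the assessors: "The evaluators will be blinded to the type of intervention that individuals will receive". Participants are given an instruction: "Individuals will be oriented to not comment to the evaluators about any details of the intervention that they will receive".

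Statistical analysis uses baseline data to describe the comparability of the groups. It also plans effect sizes for a paired t-test that assume "0.5 correlations between baseline, at the end of the trial, and at follow-up".

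**The concern.** A baseline value is useful because it cannot have been influenced by the assignment. If the arm is already fixed, and possibly known, when the pre assessment is done, that protection is lost.

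Three things are at stake:

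- **Measurement.** Limits of stability (part of the primary outcome), the 10-Meter Walk Test and the Five Times Sit-to-Stand Test depend on effort, and the PDQ-39 is self-reported. Pleasure or disappointment about the arm could move any of them. The section Interventions itself expects the two arms to motivate people differently, through company in one and novelty in the other.
- **Evaluator blinding.** It rests partly on participants keeping silent. With disclosure on Day 1, that silence must already hold at the first measurement, when there should be nothing to reveal.
- **Completeness.** A person who leaves on learning the arm is randomized, belongs in the intention-to-treat set and has no pre value.

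The Discussion says that the results will be used to calculate the sample size of a larger trial, so a distorted pre-post effect estimate would be carried forward.

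**Working it through.** The plan gives no figure for this point. The check is of the order of events, followed by which analyses could be exposed.

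**1. Are the days in Table 4 real days, and does it matter?** Days 3 to 16 are 16 − 3 + 1 = 14 entries, matching the 14 sessions. At two sessions per week these take 14/2 = 7 weeks, so the days in that range act as visit numbers. Day 17 + 30 = Day 47 agrees with the 30-day follow-up. Read as days or as visits, the order is the same: allocation, then baseline one step later, then the first session.

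**2. Does the text correct the order?**

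| Place in the protocol article | What it fixes | Baseline before allocation? |
|---|---|---|
| Table 4 | Allocation Day 1, pre assessment Day 2 | No, the reverse |
| Outcome measures | Baseline at week 0 | Silent |
| Randomization section | Eligibility, then stage block, then randomization | Silent |
| Blinding text | Evaluators blinded, participants asked for silence | Silent on when the arm is disclosed |

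Nothing shown puts baseline first or delays disclosure. Fig. 1 is not reproduced, so its order could not be checked.

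**3. Which comparisons are exposed?** Suppose knowledge of the arm shifts the baseline mean of one arm by s (in SD units), and a fraction k of that shift is still present at the post assessment. Both s and k are assumptions; the document gives neither.

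- Difference in post values: error k × s. It contains no baseline term and is the same whenever allocation takes place.
- Difference in change scores: error k × s − s = (k − 1) × s. With k = 0 this is −s; with k = 1 it is zero.
- Baseline-adjusted difference, if one were run with equal variances and the plan's correlation of 0.5: error k × s − 0.5 × s = (k − 0.5) × s. The planned differences are unadjusted, so this is for orientation only.

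The distortion thus depends on the analysis and on whether the shift fades. Because s and k are unknown, no numerical bias follows from the document.

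**4. Missing baselines.** The section Sample size plans 18 per arm. One withdrawal between Day 1 and Day 2 is 1/18 = 5.6% of an arm. How many would withdraw is unknown.

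**5. Is early allocation needed?** Stratification uses only disease stage, which is also an eligibility item and so is known at screening. The assignment can be released at any time between the Day 2 measures and the first session.

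**The case against.** The strongest reply is that Table 4 dates allocation, not disclosure. No sentence says when participants learn their arm, and the sponsor may already withhold it. This stands: the document supports that participants can know their arm at baseline, not that they do. A reader might take the future tense of the instruction to participants as proof of knowledge at Day 2. It is not proof, because the same instruction covers the post and follow-up assessments and the whole article is written in the future tense.

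A reader might also take the randomization section as confirming allocation on Day 1. It does not clearly do so. Its wording that randomization follows once individuals have been identified and placed in stage blocks can be read as a single randomization after the sample is assembled, which fits poorly with a Day 1 tick for each participant. It does not put baseline first either.

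Third, the evaluators are blinded and participants are asked not to reveal their arm. That is a genuine safeguard against assessor bias. It does not touch the participant's own effort or answers, or withdrawal before baseline.

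Fourth, the planned contrast is an unadjusted mean difference. If that means a difference in post values, a baseline shift does not enter it, so it would be wrong to say that every comparison is biased. The paired effect sizes and the baseline comparability check remain exposed.

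Finally, this is a feasibility trial without a formal sample size calculation, and one withdrawal in 18 lies within the 20% dropout allowance. The attendance, safety and acceptability outcomes do not use the pre assessment. This limits the severity but leaves the order in Table 4 as it is.

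**Conclusion.** The point holds as a defect in the stated order of events. Allocation precedes the baseline assessment in the schedule, nothing shown withholds the assignment, and the treatments cannot be masked from participants. Baseline values of effort-dependent and self-reported measures may therefore be influenced by the arm, and some randomized participants may lack them.

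The possible bias is limited to analyses that use the pre value: change scores, paired effect sizes and baseline comparability. Through these it reaches the effect estimates intended for the later trial. It does not reach a difference in post values or the attendance, safety and acceptability results, so the document gives no ground for calling those feasibility conclusions invalid.

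The size cannot be stated. For a change score it runs from nothing, if the shift persists unchanged, to the whole baseline shift, if it has gone by the post assessment. The conclusion assumes that the assignment may reach participants on Day 1 and that Fig. 1, which is not shown, does not say otherwise. It should be fixed, because analysis cannot restore a contaminated or missing baseline.

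**What to change.** 1. In Table 4, move allocation to after the Day 2 initial assessment. If it has to stay on Day 1 for logistic reasons, add a row for disclosure of the assignment to participants and staff, and place that after the initial assessment.
2. In the section Randomization, allocation concealment, and blinding, add one sentence: the assignment is released only after all baseline measures have been completed and recorded, and before the first training session.
3. In the same section, state whether randomization is done person by person or once the whole sample has been sorted by stage, so that the text and Table 4 agree.

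The cost is one table row and one or two sentences, with no extra visit and no change to the stratification. If the assignment is already withheld in practice, the change only records it.
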